### Intervention

#### Exercise

Subjects will participate in an 80-minute, group (6 per group) exercise session led by a certified exercise trainer knowledgeable in the ABC-C program for 3 days per week for 6 weeks. Trained research assistants will spot participates with high fall risk. Although the literature does not provide a clear dose–response for balance exercise intervention, there is consensus that a challenging program at higher doses (at least 2×/week) will show improvement [30, 31]. The exercise protocol is an adaptation of our ABC exercise program for PD (Table 1) [26] The theoretical basis for ABC is based on research from our laboratory and others that identified the primary neurophysiological and cognitive constraints that limit balance and mobility in PD [26, 28]. The exercises are designed as a circuit to challenge movement-skills known to be impaired in PD. Stations will include: (1) Gait training (2) PWR Moves © [32], (3) Agility course, (4) Lunges, (5) Boxing and (6) Tai Chi [33]. Each activity was chosen for its inherent focus on multi-directional movements, dynamic postural transitions, axial mobility, big movements and whole body motor sequencing. Each station is engaged for 10–20 minutes with rest periods in between stations. Each station is systematically progressed from beginning to intermediate to advanced levels by challenging: (1) divided attention with secondary cognitive tasks, (2) response inhibition, (3) limiting external sensory cues, (4) increasing speed and resistance.

**Table 1 Tab1:** Overview of exercise and education interventions

EDUCATION		EXERCISE			
Frequency	One 90 min session/week, five 30 min relaxation sessions/week at home TOTAL: 240 min/week of education and relaxation	Frequency	Three 80 min sessions/week: TOTAL: 240 min/week of exercise		
Topic	Goal	Station	Time	Goal	Progression
Resources	Topic: Finding information on PD, communicating effectively with health care providers and building a support team.	Gait training	10	Warm up, big steps, arm swing	Speed, UE support (poles), cues for big steps, ankle weights, cognitive task
Sleep, Fatigue, Pain	Topic: Solutions to common sleep, pain and fatigue problem in PD.	PWR! Moves	20	Aerobic, whole body sequencing, amplitude training	3 levels of difficulty
Nutrition	Topic: Healthy eating guidelines, normal serving sizes, nutrition, and meal planning.	Lunging	15	Multi-directional, anticipatory control, dual task, executive function	Sequences, visual cues, UE support, cognitive task
Difficult emotions, stress and depression	Topic: Solutions to common emotional ups and downs that accompany chronic illness.	Agility	10	Turns, multi-directional, cognitive task	Speed, cognitive task
Communication	Topic: Improving communication (verbal, voice tone and body language).	Boxing	10	Powerful movements, dual task, anticipatory movement, executive function	Response inhibition, hand weights, cognitive task
Medication	Topic: Purposes, effects and responsibilities of common PD related medication.	Tai Chi	15	Weight shifting, limits of stability, postural responses, step initiation	3 levels of difficulty

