### Sample Size

We computed power to detect differences between the intervention arms in a crossover trial via analysis of variance with level of significance set to 0.05 (SAS software v9.3). We assumed baseline levels and patterns of change similar to those reported in King 2013 [28]. We examined the significance of treatment effect from 1000 simulated replications of a crossover trial. The trial is comfortably powered (85 %) with 120 patients if total Mini-BESTest score increases by 2.4 points on average in the ABC arm, and only 1.3 points on average in the control arm. We predict a roughly 20 % drop-out rate, which is conservative based on our previous experience with short duration trials of rehabilitation in PD and by others [24, 25, 28, 29].

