#### Education

The Education program is a chronic disease education program to teach patients how to live better with their chronic condition. It was developed by our research team to be specific for people with PD. It will include content and discussion of topics such as sleep, nutrition, and medication management (Table 1). Classes will consist of a group of subjects (up to 6) meeting with the trainer for 90-minute session, once a week for six weeks. In order to match dose of the education intervention with the exercise intervention, participants will be provided relaxation tapes to be used at home 5 times per week for 30 minutes for an overall education dose of 240 minutes; similar to the exercise dose [34].

Compliance will be recorded at each session by the exercise trainer for both exercise and education. For the education arm, participants will record compliance for the relaxation sessions in a logbook. The trainer will code progression of exercise difficulty at the end of each week to determine the level of exercise progression for each person. Additionally, participants will state the level of perceived exertion (0–10 scale) after each exercise session. People will also wear hear rate monitor during class in order to assess the aerobic level of work being performed during exercise.

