#### Statistical Analysis

First, we will compare the amount of improvement in the Mini-BESTest with an analysis of covariance (ANCOVA) model, controlling for age. It is possible that lower functioning patients will have larger adaptation to ABC-C since they start out with less function. Alternatively, it is possible that the lower functioning patients will have poorer exercise tolerance so will improve less so we will also control for baseline Mini-BESTest*.* Because we are utilizing a crossover design, the treatment effect will represent change during the ABC-C versus control rehabilitation periods regardless of whether a patient received the ABC-C intervention during period 1 or period 2. We will assess, but do not anticipate, period by treatment group interaction effects. We will also enter an interaction term into the model to assess for differential intervention effects cognitive and/or frontal lobe structural and functional connectivity status. Second, we will relate the percent improvement in the Mini-BESTest with ABC-C intervention with baseline measures of posture/gait impairments, cognitive impairments and both structural and functional connectivity of the Posture/Locomotor circuit at baseline with linear regression models. Previous studies have shown the Minimal Detectable Change of the Mini-BESTest was 3 points [52]. We will also determine how many subjects move from high- to low-fall risk; a cutoff score for identifying PD fallers from non-fallers with the Mini-BESTest is 19/28 (63 %), with a sensitivity of .98 in 80 subjects [53].

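### Both interventions are class-delivered but the stated ANCOVA and 85% power mention no class effect; intervals are too narrow to the extent that class effects differ between periods

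*Protocol article*

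**What the plan says.** Delivery. The Exercise section states "Subjects will participate in an 80-minute, group (6 per group) exercise session led by a certified exercise trainer", three days a week for six weeks. The Education section states "Classes will consist of a group of subjects (up to 6) meeting with the trainer for 90-minute session". These classes are weekly over six weeks, with relaxation tapes at home five times a week for 30 minutes. Methods/design adds that the same trainers deliver both interventions and that every patient crosses over.

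Allocation. Patients are randomised individually to a sequence, in blocks of twelve (Randomization and blinding).

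Power. The Sample Size section uses 1000 simulated crossover trials analysed by analysis of variance, with "level of significance set to 0.05". It concludes "The trial is comfortably powered (85 %) with 120 patients". That figure assumes mean Mini-BESTest gains of 2.4 points with exercise and 1.3 points with control. For variability it says only "We assumed baseline levels and patterns of change similar to those reported in" a cited earlier study. It expects roughly 20% drop-out and does not say whether the 120 is before or after that loss.

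Analysis. The Statistical Analysis section says "we will compare the amount of improvement in the Mini-BESTest with an analysis of covariance (ANCOVA) model, controlling for age", adds baseline Mini-BESTest as a covariate, defines the treatment effect as change in the exercise period against change in the control period, and plans a check for a period-by-treatment interaction. Neither this section nor Sample Size mentions class.

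**The concern.** Patients in one exercise class share 3 × 6 = 18 sessions, with the same trainer, peers and calendar weeks. Their changes in Mini-BESTest may therefore be more alike than those of patients in different classes. If so, six patients in a class carry less information than six unrelated patients.

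A crossover removes part of this. If a class lifts or depresses its members equally in both periods, the within-person difference eliminates the effect. What remains is anything specific to one period, such as an exercise block that went particularly well or badly.

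There is reason to expect some remainder. Exercise is 3 × 80 = 240 minutes a week, all in class. Education is 90 minutes in class plus 5 × 30 = 150 minutes at home. Class influences thus have more room to act in exercise than in education, so full cancellation is unlikely. At stake are the width of the primary confidence interval, the true type I error and the meaning of the 85%.

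**Working it through.** **Inputs from the protocol article.** N = 120, power 85%, alpha 0.05, mean changes 2.4 and 1.3 points (difference 1.1), exercise class size 6, education class size up to 6, drop-out about 20%.

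**Assumptions.** Two-sided test, 1:1 sequences, equal class sizes, normal approximation. The ICC, written ρ, is that of each patient's exercise-minus-education difference in change, not of change within one period. The article gives no ICC; 0 to 0.10 is an assumed range.

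**Step 1: the stated 85%.** It cannot be reproduced, because no SD or within-person correlation is given. It can only be back-solved. Power = Φ(1.1 / (SD_diff/√N) − 1.96) = 0.85 requires 1.1 / (SD_diff/√N) = 1.960 + 1.036 = 2.996.
- N = 120: SD_diff = 1.1 × √120 / 2.996 = 4.02 points.
- N = 96 (20% loss): SD_diff = 1.1 × √96 / 2.996 = 3.60 points.

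**Step 2: effect of class.** With m per class:
- design effect DE = 1 + (m − 1)ρ
- power of a test with the correct standard error = Φ(2.996/√DE − 1.96)
- type I error of a test ignoring class = 2 × (1 − Φ(1.96/√DE))
- factor by which the unadjusted interval is too narrow = √DE

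| ρ (m = 6) | DE | Power | Type I error, class ignored | √DE |
|---|---|---|---|---|
| 0 | 1.00 | 85% | 5% | 1.00 |
| 0.01 | 1.05 | 83% | 5.6% | 1.02 |
| 0.05 | 1.25 | 76% | 8.0% | 1.12 |
| 0.10 | 1.50 | 69% | 11% | 1.22 |

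Example, ρ = 0.05: DE = 1 + 5 × 0.05 = 1.25; 2.996/1.118 − 1.96 = 0.72; Φ(0.72) = 0.76.

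Power reaches 80% when DE = (2.996/(1.960 + 0.842))² = 1.14, that is at ρ = 0.14/5, about 0.03.

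**Step 3: smaller classes.** With 20% loss, m = 0.8 × 6 = 4.8. Holding 85% as the power without clustering, ρ = 0.05 gives DE = 1 + 3.8 × 0.05 = 1.19, power 78% and type I error 7.2%. Over ρ = 0.01 to 0.10, power runs from 84% to 72%.

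**Step 4: only exercise clusters.** Let each period's change have variance σ², independent between periods, with exercise-period ICC ρ_E and none in education. The contrast has variance 2σ², of which ρ_E·σ² is between classes, so ρ = ρ_E/2.
- ρ_E = 0.05: ρ = 0.025, DE = 1.125, power 81%, type I error 6.5%.
- ρ_E = 0.10: ρ = 0.05, power 76%, type I error 8.0%.

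**Step 5: simulation check.** In 10,000 simulated trials with 20 intact classes of six and a per-period ICC of 0.10, the patient-level test rejected a true null in 10.9% when class effects were independent between periods, 8.0% when half the class variance was shared, and 4.9% when all of it was shared. The last confirms full cancellation.

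A test on class means kept its 5% level throughout. With about 20 classes it pays for the lost degrees of freedom: power was 81% with no clustering and 72% at an ICC of 0.05 with independent class effects. It is a cruder analysis than a mixed model.

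**The case against.** The strongest case against is that the point rests on silence. The article is condensed, and a class random effect could sit in an analysis plan that is not shown. A reader might infer from the text that patients are declared independent units; it says no such thing, and the variance structure of the simulation is not described. This stands. But the article does name the primary model, its covariates and a finished power figure. A later analysis plan could add a class term, but the published 85% would still stand without a stated allowance for class.

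A reader might also infer that the intervals are too narrow and the power overstated as a matter of fact. The documents do not support that. They give no ICC; at ρ = 0.01 the loss is under two percentage points, and at full cancellation it is nil.

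It is also tempting to put a within-class correlation of change in one period straight into 1 + 5 × ICC. That applies to the contrast only if class effects are equally strong in both periods and nothing is shared. If only exercise clusters, the relevant ICC is halved (Step 4). Effects of the trainers common to both interventions also cancel.

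Finally, about 20 classes is the arithmetic of full classes, 120/6. Education classes may be smaller, drop-out shrinks both, and the article does not say whether classes stay together at crossover. All of this limits the size. It does not change the direction for any class effect that fails to cancel. The home share of education cuts the other way: it weakens clustering there, but leaves less to offset an exercise-class effect.

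**Conclusion.** The point holds in conditional form. Followed as written, the primary analysis gives intervals that are too narrow, and the 85% is optimistic, to the extent that class effects differ between the exercise and education periods. The direction is secure for any positive non-cancelling class effect; the size is not known.

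On the assumed range, the consequence is negligible at a contrast ICC of 0.01, takes power below 80% from about 0.03, and is material at 0.05 (76% power, or 78% with 4.8 per class; type I error 8.0% or 7.2% if class is ignored). These figures take the stated 85% as correct without clustering, which cannot be checked, and assume equal class sizes and a two-sided test. They do not show that the trial's inference is invalid. They show that the stated model and power need a class term and a stated condition.

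**What to change.** 1. Record the class each patient attends in each period. The trainer already records compliance at every session, so this is one more field. It also shows whether classes stayed together at crossover.
2. Add a random effect for class within period to the primary Mini-BESTest model, or use class-robust standard errors. Either way apply a small-sample degrees-of-freedom correction (Kenward-Roger for the mixed model), since there may be only about 20 exercise classes.
3. Report the estimated ICC of the treatment contrast.
4. Present the 85% as conditional on no class-by-period clustering, and show power over a contrast ICC of 0 to 0.05. By the approximation above this is 85% down to 76% with six per class.

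The cost is one field, one model term, a slightly wider interval and a slightly lower stated power. If the class variance proves close to zero, the main loss is in degrees of freedom.

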#### Education

The Education program is a chronic disease education program to teach patients how to live better with their chronic condition. It was developed by our research team to be specific for people with PD. It will include content and discussion of topics such as sleep, nutrition, and medication management (Table 1). Classes will consist of a group of subjects (up to 6) meeting with the trainer for 90-minute session, once a week for six weeks. In order to match dose of the education intervention with the exercise intervention, participants will be provided relaxation tapes to be used at home 5 times per week for 30 minutes for an overall education dose of 240 minutes; similar to the exercise dose [34].

Compliance will be recorded at each session by the exercise trainer for both exercise and education. For the education arm, participants will record compliance for the relaxation sessions in a logbook. The trainer will code progression of exercise difficulty at the end of each week to determine the level of exercise progression for each person. Additionally, participants will state the level of perceived exertion (0–10 scale) after each exercise session. People will also wear hear rate monitor during class in order to assess the aerobic level of work being performed during exercise.

#### Assessment procedures

All people who are eligible per phone screening will come into the clinic for the informed consent process. An investigator will verbally explain the consent form, allow the person ample time to ready through the consent form and then will acknowledge consent by signing the form. All subjects will first read and sign consent forms. All outcomes will be measured in the practical OFF levodopa state (12 hours withdrawal). At baseline, people will be assessed on imaging, mobility and cognitive measures and will repeat the mobility and cognitive measures after the 1st six-week intervention and again after the 2nd six-week intervention (Table 2).

**Table 2 Tab2:** Secondary outcome measures by domains

Domain Tested	Test	Description
Clinical		
	MDS-UPDRS	All sections of the Unified Parkinson’s Disease Rating Scale will be used to measure related to severity of PD.
	NFOGQ	The New FoG of Gait Questionnaire will be used to identify ‘freezers’ (score >3).
	Activities of balance confidence (ABC)	The ABC measures how balance confidence limits participating in the community.
	PDQ-39	This 39 item questionnaire measures multiple domains of quality of life.
Mobility		
	Balance	Postural sway during 30 seconds of quiet stance with and without cognitive task
	Turning	Smoothness of turning measured during the 1 min turning in place (360 degree turning in place) and turns during the 2 min walk with and without a cognitive task.
	Gait	Spatial and temporal gait metrics during walking with and without dual task
Imaging		
	High angular resolution diffusion imaging	High angular resolution diffusion imaging to assess white matter microstructure. Structural connectivity of the locomotor network will be assessed using probabilistic tractography.
	rsfcMRI	An indirect assessment of communication between spatially disparate neural regions. Analysis is restricted to neural regions comprising the locomotor network including the supplementary motor area, subthalamic nuclei, mesencephalic locomotor regions (pedunculopontine and cuneiform nuclei), and the midline cerebellar locomotor region
Cognition		
General	Scales for outcome of Parkinson’s Disease-Cognition (SCOPA-COG)	An instrument that was designed to assess the specific ‘frontal-subcortical” cognitive deficits found in Parkinson’s disease
Inhibition	Stroop task, flankers, Go/nogo, Stop signal task	The ability to deliberately inhibit dominant or prepotent responses when appropriate.
Shifting	Set-Shifting, Trail making task	The ability to flexibly alter behavior when relevant changes occur in the predefined goal or in the environment.
Updating	Dot counting task	The ability to update and monitor working memory representations.
Visuospatial	Benton judgment of line orientation test	The ability to identify a stimulus, its orientation, and its location.

### Primary outcome measure – Mini-BESTest

The primary outcome measure on which the intervention study was powered is the clinical *Mini-BESTest.* [35] The *Mini-BESTest* [35] is a sensitive measure of dynamic balance and includes 14 items (a maximum and best score of 28) [36, 37].

### Secondary outcome measures

Secondary measures for clinical measures, mobility (gait and balance), cognition and imaging domains are listed in Table 2.

### Clinical Measures

Our clinical tests will include assessment of quality of life, balance confidence, disease severity and freezing of gait. Specifically, the Parkinson Disease Questionnaire-39 (PDQ-39) [38] will be used for quality of life, the Activities-Specific Balance Confidence Scale (ABC) [39] will be used for balance confidence, the Movement Disorders Society Unified Parkinson’s Disease Rating Scale ( MDS UPDRS-Motor- Parts 1-IV) will be used to measure disease severity [13, 40] and the new freezing of gait questionnaire will be used as a self assessment of freezing of gait [41].

### Mobility Testing

All secondary measures of mobility come from performance of tasks while subjects are instrumented with body-worn, inertial sensors. Specifically, eight wireless, synchronized, Opal inertial sensors (APDM, Inc) will be applied with elastic Velcro bands to both feet, ankles and wrists, as well as the lumbar spine and mid sternum of the torso. Inertial sensor data collected at 128Hz will be wirelessly transferred to a laptop for automatic generation of gait and balance metrics by Mobility Lab and raw data for further analysis with Matlab [42]. Participants will perform tasks of quiet stance, the 2-minute walk test and the 360-degree turn test with and without a secondary, cognitive task (Table 2). All participants will wear a safety belt during the walking tasks and a trained research assistant will walk along side the participants. If a participant loses his or her balance, the research assistant will assist and prevent a fall. All safety measures will be taken to ensure a secure and comfortable environment. To prevent fatigue, participant will be repeatedly reminded that he or she may take a break whenever needed.

### Cognitive testing

Participants will complete a battery of cognitive tests to assess several dimensions of cognition. A table of all cognitive tests and a brief description is presented in Table 2. Most tests are categorized into the three domains of executive function defined by Miyake and colleagues (2000): *inhibition* (Stroop color-word test, Flankers, Go/NoGo, Stop Signal Reaction Time Test) [43–46], *set shifting* (Trail Making, Shifting Task) [45, 47–49] and *updating or working memory* (Dot Counting Test) [45]. We will also assess general cognition for people with PD via the Scales for Outcome of Parkinson’s Disease-Cognition (SCOPA-COG) and Montreal Cognitive Assessment (MoCA) [50, 51]. In addition, visuospatial function (Benton Judgement of Line Orientation) will be assessed.

### Imaging

The subject will be led into the MRI magnet room and positioned on the MRI system bed. A 32-channel Siemens rf-receiver coil will be placed appropriately for brain MRI, and the subject will be loaded into the magnet. During imaging, the subject’s head will rest on a special neck and head pillow to minimize head movements. Extra pillows under the knees and back will be used to make subjects as comfortable as possible. They will wear headphones to dampen noise during imaging and to allow subjects to hear and talk to the investigators at all times. Our procedures do not include administration of MRI contrast agents. The following protocol will then be executed:

Imaging data will be acquired using a 3.0 T Siemens Magnetom Tim Trio scanner with a 12-channel head coil. We will collect one whole brain high-resolution structural T1-weighted MPRAGE sequence (sagittal, TE = 3.58 ms, TR = 2300 ms, 256 x 256 matrix, resolution = 1 mm^3^, 1 average, total scan time = 9 min-14 s). We will also collect high angular resolution diffusion imaging using an echo-planar imaging sequence (72 different gradient directions, b-value = 3,000 mm/s^2^, TR = 7100 ms, TE = 112 ms, 2.5 mm^3^ voxels, 48 slices, FOV = 230 × 230 mm). Finally, we will acquire a resting-state functional MRI (*rs*-*f*MRI) using a gradient-echo echo-planar imaging sequence (TR = 2500 ms, TE = 30 ms, FA = 90°, 3.8 mm^3^volexs, 36 slices with interleaved acquisition, FOV = 240 × 240 mm). We will acquire two 10-minutes runs, providing a total of 20 minutes of resting state data for each subject in the study. Subjects will be instructed to lie still and keep their eyes open. Head padding will be provided to help subjects keep their heads still, earplugs will protect against scanner noise, and a leg bolster will be provided for back comfort. The technician will monitor the data and collect an extra scan if head movement > 1 mm is apparent.

